**Fig. 1 Fig1:**
[figure not shown]
Flowchart of study

### Intervention design

#### Intervention description

The intervention will be delivered in a face to face group format onsite at participating schools. The intervention will be 10 × 50–60 min sessions, once per week for 10 weeks. Each intervention session will include:
Psycho-education – guided group based discussion. Topics include respect, goal-setting, self-concept and self-esteem, courage, resilience, bullying and peer pressure, self-care and caring for others, values, and, optimism and hope;Warm up – including jogging, star jumps, push ups, and sit ups;Stretching – including hamstring stretch, triceps stretch, figure four stretch, butterfly stretch, lunging hip flexor stretch, knee to chest stretch, and standing quad stretch; and,Technical practice – including stances, blocks, punching, and kicking.

Additionally, intervention sessions intermittently include (alternated throughout the program):
(e)Patterns practice – a pattern is a choreographed sequence of movements consisting of combinations of blocks, kicks, and punches performed as though defending against one or more imaginary opponents;(f)Sparring – based on tai-chi sticking hands exercise (which has been included as an alternative to traditional martial arts sparring); and(g)Meditation – based on breath focusing exercise.

In the final session the intervention will conclude with a formal martial arts grading where participants will be awarded a yellow belt subject to demonstration of martial arts techniques (stances, blocks, punching, and kicking) and the pattern learnt during the program. While it is desirable for participants to attend all 10 sessions to achieve intervention dose, it is unrealistic to assume all sessions will be attended. Research has suggested that determining an adequate intervention dose in health promotion programmes can be based on level of participation and whether participants did well [15]. In the current study intervention dose will be assumed if participants successfully complete the formal grading and are awarded a yellow belt. It is important to note that aggressive physical contact is not part of the intervention program. The intervention will be delivered by a (1) registered psychologist with minimum 6 years’ experience, and (2) 2nd Dan/level black-belt taekwondo instructor with minimum 5 years’ experience. Materials used during the intervention will include martial arts belts (white and yellow), and martial arts training equipment (for example strike paddles, strike shields).

#### Theoretical framework

The intervention development and implementation will be based on a traditional martial arts model, dichotomous health model, and social cognitive theory. Research examining the relationship between the martial arts and mental health has typically used a bipartite model [16] which distinguishes between traditional and modern martial arts. The intervention is based on a traditional martial arts perspective, which emphasizes the non-aggressive aspects of martial arts including psychological and philosophical development [17].

The absence of an explicit health model is a significant methodological limitation of previous research examining the mental health outcomes of martial arts training. The dominant models of mental health are based on the homeostatic assumption that normal health reflects the tendency towards a relatively stable equilibrium; and that the dysregulation of homeostatic processes causes ill-health [18]. These models can be defined dichotomously as having a: (1) pathological basis (deficit model) which refers to the presence or absence of disease based symptoms such as depression or anxiety; and (2) wellbeing basis (strengths model) which refers to the presence or absence of beneficial mental health characteristics such as resilience or self-efficacy. While considering both aspects of the mental health continuum, this study was particularly interested in the strengths model and examined the wellbeing characteristics of resilience and self-efficacy.

Social cognitive theory suggests that knowledge can be acquired through the observation of others in the context of social interactions, experiences, and media influences; and explains human behaviour in terms of continuous reciprocal interaction between personal cognitive, behavioural, and environmental influences [19]. The theory is useful for explaining the learning processes in the martial arts, which include: (a) modelling – where learning occurs through the observation of models; (b) outcome expectancies – to learn a modelled behaviour the potential outcome of that behaviour must be understood (for example, the anticipation of rewards or punishment); and (c) self-efficacy – the extent to which an individual believes that they can perform a behaviour required to produce a particular outcome [19].

The study’s theoretical framework incorporating a traditional martial arts model, dichotomous health model and social cognitive theory facilitates examination of the effects of martial arts training on mental health, ranging from mental health problems to factors associated with wellbeing such as resilience and self-efficacy. Further, the framework may determine the efficacy of martial arts training as an alternative mental health intervention that improves mental health outcomes.

### Outcomes

Evaluation of the intervention program will involve a variety of standardised psychometric instruments to report on mental health related outcomes. Instruments include the Strengths and Difficulties Questionnaire (SDQ) [20], Child and Youth Resilience Measure (CYRM) [21], and Self-Efficacy Questionnaire for Children (SEQ-C) [22]. All outcome time-points will be examined 1 week pre-intervention, 1 week post-intervention, and 12-week post-intervention (follow-up).

#### Behavioural and emotional difficulties

The primary outcome measured by the SDQ will be mean total difficulties. Additionally, the SDQ will measure the following secondary outcomes: emotional difficulties, conduct difficulties, hyperactivity difficulties, peer difficulties, and pro-social behaviour.

Total difficulties was selected as a primary outcome as it provides an overview of participants’ psychological problems. The SDQ scale is a commonly used psychometric screening tool recommended for use by the Australian Psychological Society [23] and has been normed for the Australian population.

#### Resilience

The primary outcome measured by the CYRM will be mean total resilience. Additionally, the CYRM will measure the following secondary outcomes: individual capacities and resources, relationships with primary caregivers, and contextual factors.

Resilience was selected as a primary outcome as it is a current focus of research regarding psychological strengths, but has not been examined regarding the effect of martial arts training. The CYRM-28 was used in the study as it efficiently operationalises the theoretical aspects of resilience in a valid and reliable manner, but is shorter than comparable scales (for example the Resilience Scale for Children and Adolescents [24]).

#### Self-efficacy

The primary outcome measured by the SEQ-C will be mean total self-efficacy. Additionally, the SEQ-C will measure the following secondary outcomes: academic self-efficacy, social self-efficacy, and emotional self-efficacy.

Self-efficacy was selected as a primary outcome as this operationalised a relevant component of social cognitive theory, which is important regarding the hypothesised learning processes in the intervention. The SEQ-C was used in the study as it operationalises self-efficacy for adolescents in an educationally relevant context.

### Statistical methods

Statistical analysis of the primary and secondary outcomes will be conducted using SPSS statistics version 25 (IBM SPSS Statistics, 2017) and alpha levels will be set at *p* < 0.05.

The collected psychometric test data will be consolidated into subscale variables using factor analysis and the internal consistency of each variable will be examined to determine reliability. Items to be included in the scale variables will be added and computed to create composite scores. Repeated measures univariate analysis of variance (ANOVA), and multivariate analysis of variance (MANOVA) will primarily be used to analyse test data. Ordinal regression will be used to analyse test data based on psychometric measures using a 3-point Likert scale. Interpretation of effect sizes will reflect Cohen’s suggested small, medium, and large effect sizes, where partial eta squared sizes are equal to 0.10, 0.25, and 0.40 respectively [25].

Age, school grade level, sex, socio-economic status and cultural background will be included as covariates in the analysis.

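### Three co-equal primary outcomes share one undivided 0.05 level with no decision rule; if any one suffices, the false-claim risk is about 11–14%, not 5%

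*Protocol article*

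**What the plan says.** Three subsections under Outcomes each designate a primary outcome:

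- Behavioural and emotional difficulties: "The primary outcome measured by the SDQ will be mean total difficulties".
- Resilience: "The primary outcome measured by the CYRM will be mean total resilience".
- Self-efficacy: "The primary outcome measured by the SEQ-C will be mean total self-efficacy".

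Each total has its own rationale, and none is placed above the others. The same subsections list the secondary outcomes: five from the SDQ ("emotional difficulties, conduct difficulties, hyperactivity difficulties, peer difficulties, and pro-social behaviour"), three from the CYRM ("individual capacities and resources, relationships with primary caregivers, and contextual factors") and three from the SEQ-C ("academic self-efficacy, social self-efficacy, and emotional self-efficacy").

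Statistical methods covers both classes in one sentence, with the level fixed at p < 0.05; it opens: "Statistical analysis of the primary and secondary outcomes will be conducted using SPSS statistics version 25 (IBM SPSS Statistics, 2017) and alpha levels will be". It names repeated measures ANOVA and MANOVA as the main methods, without saying which one decides a primary outcome or whether one is a gate for the other. Sample size calculation also uses 0.05 undivided, with 90% power and d = 0.3, giving 117 completers per group.

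**The concern.** The aim, as given in the Background and Discussion, is a general one about mental health outcomes, and the Conclusion anticipates effects on public health and school policy. Three primary tests feed that single broad claim. The article does not say whether one, a particular one or all three must be significant. A reader following the plan as written could announce success on whichever total falls below 0.05. In that case 5% is the error rate of each test, but not of the trial's main conclusion. The article criticises earlier martial arts research for its methods and presents its own evaluation as rigorous, so its error control should be explicit.

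**Working it through.** **Inputs.** Three primary totals (Outcomes). Secondary outcomes: 5 + 3 + 3 = 11 (Outcomes). Level 0.05 (Statistical methods and Sample size calculation). 117 completers per group, d = 0.3, 90% power, 20% dropout (Sample size calculation). Two-sided tests are assumed, since sidedness is not stated. Controls are not measured at follow-up (Study design), so each primary outcome has one randomised between-arm comparison, at post-intervention.

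**The plan's own figure.** ((1.960 + 1.282)/0.3)² = 116.7, which rounds up to 117 per group and 234 in total; 234/0.8 = 292.5, rounded up to 293. Both published figures are reproduced with one test at the full 0.05, so no part of the sample size allows for three primary outcomes.

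**Chance of at least one false primary claim if any one suffices.** For independent tests this is 1 − 0.95³ = 0.143. For equally correlated test statistics it is one minus the probability that all three stay within ±1.960 under a trivariate normal distribution:

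| Assumed correlation | At least one of three below 0.05 |
|---|---|
| 0 | 14.3% |
| 0.3 | 13.6% |
| 0.5 | 12.5% |
| 0.7 | 10.9% |
| 0.8 | 9.8% |
| 0.9 | 8.4% |

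**With a correction.** At 0.05/3 = 0.0167 each, the family-wise rate is 1 − (1 − 0.0167)³ = 4.9% if the outcomes are independent and 4.4% at correlation 0.5.

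**Effect on power.** Take a between-arm difference of d = 0.3 with 117 per arm and no baseline adjustment. The expected test statistic is 0.3 × √(117/2) = 2.295.

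- At 0.05: Φ(2.295 − 1.960) = 63%.
- At 0.0167, Holm's first step: Φ(2.295 − 2.394) = 46%, or 45% with the t distribution.

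The correction therefore costs about 17 percentage points. The gap between 63% and the stated 90% has another cause: 117 per group comes from a one-sample (paired) formula, not a two-arm one. That is a separate sample-size matter.

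**Cost in numbers.** Keeping 90% power at 0.0167 multiplies the sample size by ((2.394 + 1.282)/(1.960 + 1.282))² = 1.29. On the article's own formula, 117 becomes 151 per group (150.1 rounded up), which is 302 completers and 302/0.8 = 377.5, so 378 recruited.

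**The case against.** The strongest reply is that the inflation depends on a decision rule the article never states. If all three totals had to be significant, there would be no inflation. If each total supported only a claim about its own construct, each claim would keep its 5% rate. The Theoretical framework and Outcomes sections do give separate reasons for measuring difficulties, resilience and self-efficacy. This stands as a limit on the claim: the 11–14% is conditional. It does not remove the point, because the article adopts neither rule and gathers the three totals under one aim.

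A second reply is that an analysis plan, not shown here, may contain an adjustment. It may, and the lack of a multiplicity paragraph in a condensed article would not be a finding. But this article does not leave alpha open. It sets 0.05 for both outcome classes and sizes the trial on it, so a later adjustment would alter the basis of the published sample size.

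Some stronger readings are tempting but unsupported:

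- A reader might multiply up all 14 tests and quote 1 − 0.95¹⁴ = 51%. That treats totals as independent of subscales from the same instruments, which is not credible; at correlation 0.5 the figure is about 35%. It also mixes secondary outcomes into a question about primary claims.
- A reader might infer that naming both ANOVA and MANOVA gives every primary outcome two chances of significance. The article does not say that both are applied to the same totals; MANOVA could serve the subscales. Nor can MANOVA be counted as protection: no gate is stated, and a gate would control error only when no outcome is affected.
- A reader might attribute the whole fall from 90% to 45% power to multiplicity. Most of it, from 90% to 63%, is the separate sample-size issue.

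**Conclusion.** The point holds in conditional form. The article fixes three co-equal primary outcomes, one common 0.05 level and a sample size at that undivided level, with no ranking, adjustment or success rule. If any one positive total can carry the conclusion, the chance of at least one false primary claim is about 11–14% for correlations between 0.7 and 0. This rests on that reading, on two-sided tests and on assumed correlations, since the documents give none. The direction does not depend on the correlation chosen: even at 0.9 the rate is about 8%. The plan should be changed, and the change is inexpensive if a fixed sequence is chosen.

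**What to change.** In Statistical methods, state that the three totals are controlled at a family-wise 0.05, by one of two routes:

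- a fixed sequence starting with SDQ total difficulties, which leaves the first test at 0.05 and allows later claims only if the earlier ones succeed; or
- Holm's procedure, which needs no ordering but starts at 0.0167.

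Report the 11 subscales as supportive, with intervals and no confirmatory claims. Name the one model per primary outcome that carries the decision. If the intention is instead that all three totals must be positive, or that each supports only a claim about its own construct, saying so would also settle the point.

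In Sample size calculation, state power at the alpha actually used. The edit is a few sentences across two sections. The price is a stricter or later threshold for some claims and a less favourable stated power: under Holm's first step about 45%, against 63% at 0.05, for 117 per arm, a between-arm d = 0.3 and no baseline adjustment. Keeping 90% power at that step would need about 1.29 times the sample. The fixed sequence avoids this cost for the first outcome.

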**Methods/design:**

The study is a 10-week secondary school-based intervention and will be evaluated using a randomised controlled trial. Data will be collected at baseline, post-intervention, and 12-week follow-up. Power calculations indicate a maximum sample size of *n* = 293 is required. The target age range of participants is 11–14 years, who will be recruited from government and catholic secondary schools in New South Wales, Australia. The intervention will be delivered in a face-to-face group format onsite at participating schools and consists of 10 × 50–60 min sessions, once per week for 10 weeks. Quantitative outcomes will be measured using standardised psychometric instruments.

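### Subscales are to be built by factor analysis of the trial's own data, which conflicts with the named subscales of the standardised instruments; score by the published keys instead

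*Protocol article*

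**What the plan says.** All references are to the protocol article.

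- **Abstract, Methods/design:** "Quantitative outcomes will be measured using standardised psychometric instruments". The opening of Outcomes repeats this: "Evaluation of the intervention program will involve a variety of standardised psychometric instruments to report on mental health related outcomes".
- **Behavioural and emotional difficulties:** "The primary outcome measured by the SDQ will be mean total difficulties". The secondary outcomes from the same questionnaire are "emotional difficulties, conduct difficulties, hyperactivity difficulties, peer difficulties, and pro-social behaviour". The SDQ is also said to be an instrument that "has been normed for the Australian population".
- **Resilience and Self-efficacy:** these follow the same pattern. Each has one primary total (CYRM, SEQ-C) and three named subscales. The CYRM-28 is supported by a statement that it is valid and reliable.
- **Statistical methods:** "The collected psychometric test data will be consolidated into subscale variables using factor analysis"; then "the internal consistency of each variable will be examined to determine reliability"; then "Items to be included in the scale variables will be added and computed to create composite scores".

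Statistical methods does not mention the instruments' own scoring keys.

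**The concern.** A standardised instrument has its scoring fixed before the trial: which items form each subscale, and how they are combined. Its norms and validity evidence belong to that scoring. The Outcomes section relies on this when it names the subscales and cites the instruments' properties. Statistical methods instead makes factor analysis of the collected responses the step that produces the subscale variables.

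If that is done, the variables analysed may not be the outcomes the article names. A subscale could lose items or gain items from another subscale, and the factor solution need not return the named number of subscales. A reader could then not tell whether a result for, say, conduct difficulties refers to the published subscale or to one particular to this sample. Results would also be harder to set beside norms or other trials that use the same instruments.

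**Working it through.** The article states no figure on this point, so the main check is to set the sections side by side.

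**Step 1. Count the outcomes fixed in advance.** Named subscales: 5 (SDQ) + 3 (CYRM) + 3 (SEQ-C) = 11. Primary totals: 3. Together 11 + 3 = 14.

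**Step 2. Compare the two definitions.**

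| | Outcomes section | Statistical methods |
|---|---|---|
| Source of subscales | Named parts of standardised instruments | Factor analysis of collected data |
| Item membership | Fixed by the instrument | Items to be included, list not fixed |
| Role of reliability | Cited in support of the CYRM-28 | Examined in trial data, no consequence stated |

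Both columns can define the same variable only if the factor analysis merely confirms the published structure. The text makes it the means of forming the variables, and the reliability check is a separate clause.

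**Step 3. Trace the reach.** The factor-analysis sentence speaks of subscale variables, so it bears directly on the 11 secondary outcomes. The primary totals are reached only through the later sentence on scale variables, and only if an item is left out. An unchanged item set gives an unchanged total, however the items are grouped.

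**Step 4. Does this by itself affect type I error?** A factor solution from pooled responses does not use allocation. If one solution is fixed blind to arm, swapping the arm labels under the null leaves the scoring unchanged, so the test keeps its level. What changes is the quantity measured. This argument would need a second look if follow-up responses entered the solution, because Study design says controls are not measured at follow-up. The article does not say that they would enter.

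**Step 5. Illustration of the conditional risk.** Assumptions, not trial figures: 20 items; item response = √h·f + √(1−h)·e, with f and e standard normal; communality h = 0.15 or 0.30; no arm effect; two-sample t-test at 5%; 4,000 replicates. The 117 per arm comes from Sample size calculation. Four scorings were compared: all 20 items; the 0.75 × 20 = 15 items loading highest on the first component; the 0.50 × 20 = 10 highest; and the component score.

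| h | Fixed total | Smallest p of the four |
|---|---|---|
| 0.15 | 0.0515 | 0.079 |
| 0.30 | 0.0505 | 0.069 |

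The Monte Carlo standard error at 5% is √(0.05 × 0.95 / 4000) = 0.0034, so the fixed total is at its nominal level. The rise to about 7–8% comes from taking the smallest of four p-values. Statistical methods describes no such practice.

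**The case against.** The strongest reply is that the wording is loose and the intention ordinary. The subscales are named and numbered in advance, the instruments are called standardised, and no rule for removing or moving items is given. The sentence on summing items could describe routine scoring, and the factor analysis could be a confirmatory check. That reading is possible, but it is not what the sentence says, and if it is intended, the same short clarification settles the matter.

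Other parts of the objection stand and limit the point:

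- A reader might infer that the primary totals are directly contradicted. They are not. The effect on them depends on items being dropped, which the article does not state.
- A reader might infer that items would be selected using post-intervention data from unblinded arms. The article specifies neither the time-point of the factor analysis nor whether the analysts are blinded.
- Rotation, retention rule and loading cut-offs are details that an article may leave to a fuller document. Their absence is not the fault raised here.
- The SDQ's norming is given as a property of the scale, not as the reason total difficulties became a primary outcome, and no planned analysis uses norms. Losing them would harm comparability outside the trial, not the comparison between randomised arms.

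**Conclusion.** The point holds as a conflict between two statements in the article, and it should be corrected. Its direct reach is the 11 secondary subscales, whose item content would depend on the trial's data. It extends to the three primary totals only if items are dropped. The norms cited for the SDQ and the validity cited for the CYRM-28 would then not apply to the scores analysed.

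The size cannot be computed, because it depends on how many items would move or be removed, and nothing in the article indicates that. It would be tempting to conclude that the plan inflates type I error. The document does not show this. The 7–8% above rests on an assumed item model and on picking the best of four scorings after seeing results. The verdict takes the factor-analysis sentence at its plain meaning, as the step that forms the variables; if only a check was meant, what remains is a wording fault with the same remedy.

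**What to change.** Replace the scoring sentences in Statistical methods with a statement that the SDQ, CYRM-28 and SEQ-C totals and subscales are scored by the instruments' published keys, and that these scores are used in all primary and secondary analyses. Add that internal consistency, and any confirmatory factor analysis on baseline data, are reported as description or as a sensitivity analysis and cannot change which items belong to a scale.

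This takes a sentence or two, changes neither data collection nor sample size, and removes some analysis work. The small downside is that a subscale with low reliability in this sample is reported as it stands, with its reliability beside it.

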## Methods/design

### Study design

This study is a 10-week secondary school-based intervention and will be evaluated using a randomised controlled trial. Ethics approval has been sought and obtained from an Australian University Human Research Ethics Committee, the New South Wales (NSW) Department of Education, and the Catholic Education Diocese of Parramatta. The study is registered with the Australian and New Zealand Clinical Trials Registry (ACTRN12618001405202). The study protocol was also reviewed externally by school psychologists employed by the NSW Department of Education.

Researchers will conduct baseline assessments at participating schools after the initial recruitment processes. Following baseline assessments and randomisation, the intervention group will receive the intervention after which post-intervention assessment will be conducted. A 12-week post-intervention (follow-up) assessment will also be conducted. The control group will receive the same intervention program after the first post-intervention assessment and will not be measured at follow-up. The design, conduct and reporting of this study will adhere to the Consolidation Standards of Reporting Trials (CONSORT) guidelines for a randomised controlled trial [13]. Participants and caregivers will provide written informed consent.

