### Sample size calculation

Power calculations were conducted to determine the sample size required to detect changes in mental health related outcomes resulting from martial arts training. Statistical power calculations assumed baseline-post-test expected effect size gains of *d* = 0.3, and were based on 90% power with alpha levels set at *p* < 0.05. The minimum completion sample size was calculated as *n* = 234 (intervention group: *n* = 117, control group: *n* = 117). As participant drop-out rates of 20% are common in randomised controlled trials [14], the maximum proposed sample size was *n* = 293 (intervention group: *n* = 147, control group: *n* = 146).

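### The main analysis omits adjustment for each outcome's baseline score, so the randomised comparison is a change-score test: valid, but less precise than baseline-adjusted ANCOVA on the same data

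*Protocol article*

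**What the plan says.** The article's Statistical methods section names the main method: "Repeated measures univariate analysis of variance (ANOVA), and multivariate analysis of variance (MANOVA) will primarily be used to analyse test data". One exception follows: "Ordinal regression will be used to analyse test data based on psychometric measures using a 3-point Likert scale". The covariates are then fixed for the analysis as a whole: "Age, school grade level, sex, socio-economic status and cultural background will be included as covariates in the analysis". No outcome's own baseline score appears there.

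Two other sections determine what this analysis can compare. Study design places baseline assessment before randomisation and states: "The control group will receive the same intervention program after the first post-intervention assessment and will not be measured at follow-up". Sample size calculation gives the effect and error rates: "Statistical power calculations assumed baseline-post-test expected effect size gains of *d* = 0.3", and the calculations "were based on 90% power with alpha levels set at *p* < 0.05". It arrives at 117 completers per arm (234 in all) and raises the total to 293 for 20% drop-out.

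**The concern.** Each pupil's score is measured before allocation on every primary outcome. Repeated-measures ANOVA uses that score as one of the repeated outcomes and not as a predictor. With only two shared time points this fixes the slope of post on baseline at 1. ANCOVA estimates the slope from the data. Unless the true slope is 1, fixing it there adds noise to the treatment contrast.

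What is at stake is precision that the trial has already paid for. If the correlation is modest, the planned test can be weaker even than comparing post-intervention scores alone. A smaller matter of validity arises if pupils who drop out differ at baseline in a way that is not the same in the two arms.

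**Working it through.** **Inputs.** From Sample size calculation: d = 0.3, 90% power, alpha 0.05, 117 completers per arm, 20% drop-out. Assumed, because the article does not give them: two-sided testing; d in raw-score SD units; equal SD at baseline and post; and the correlation r, shown as a range.

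**The plan's own figure.** With z-values 1.960 + 1.282 = 3.2415:

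- (3.2415/0.3)² = 116.7, so 117. This matches the stated number per arm, but it is the formula for a within-group change.
- 2 × (3.2415/0.3)² = 233.5, so 234 per arm for a between-arm comparison at d = 0.3.
- 117 per arm is enough for a between-arm test only with an unstated correlation: r = 0.75 for a change score, since 2(1-0.75) = 0.5, or r of about 0.71 for ANCOVA, since 1-0.71² is about 0.5.
- 234/0.8 = 292.5, so 293. The drop-out step reproduces.

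The origin of 117 is a separate question. Here it serves only as the number per arm that the plan expects to analyse.

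**Step 1: the planned test is a change-score test.** Only baseline and post-intervention are observed in both arms. For one outcome at two time points, the group-by-time F equals the square of the two-sample t on change. In a simulated data set of 117 per arm, both came to 23.7143. The demographic covariates do not alter this: the slope on baseline is still 1, and r is then read as the correlation given those covariates.

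**Step 2: variances**, in units of the raw-score variance.

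- Change score: 2(1-r)
- ANCOVA: 1-r²
- Difference: 2(1-r) - (1-r²) = (1-r)², which is positive for every r below 1
- Ratio, ANCOVA to change score: (1-r²)/(2(1-r)) = (1+r)/2

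**Step 3: power at 117 per arm** (noncentral t, two-sided 0.05). The effective effect is 0.3/√(2(1-r)) for change and 0.3/√(1-r²) for ANCOVA.

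| r | 2(1-r) | 1-r² | ratio | power, change | power, ANCOVA |
|---|---|---|---|---|---|
| 0.3 | 1.40 | 0.91 | 0.65 | 0.489 | 0.668 |
| 0.5 | 1.00 | 0.75 | 0.75 | 0.627 | 0.751 |
| 0.6 | 0.80 | 0.64 | 0.80 | 0.724 | 0.815 |
| 0.7 | 0.60 | 0.51 | 0.85 | 0.839 | 0.892 |
| 0.8 | 0.40 | 0.36 | 0.90 | 0.951 | 0.968 |

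Comparing post scores alone has power of about 63% whatever r is, so below r = 0.5 the change score does worse than ignoring baseline. The change score needs 1/ratio times as many pupils as ANCOVA for equal power: 54% more at r = 0.3, 33% at 0.5, 18% at 0.7 and 11% at 0.8.

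**Step 4: the other reading of d.** If 0.3 is instead standardised by the SD of change, change-score power is about 63% at every r. The ANCOVA effect becomes 0.3 × √(2/(1+r)), giving power of 81% at r = 0.3, 75% at 0.5, 70% at 0.7 and 67% at 0.8. The levels move, but the variance ratio and its direction do not.

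**Step 5: drop-out related to baseline.** Suppose completers' mean baseline differs between arms by Δ, and drop-out depends on nothing beyond baseline and arm. The change-score contrast then estimates the true effect minus (1-r)Δ, while ANCOVA estimates the true effect. Simulation agrees. With a true effect of -0.30, about 20% loss per arm, and the loss related to baseline in the intervention arm only, the change score gave -0.25 (r = 0.5) and -0.27 (r = 0.7), and ANCOVA gave -0.30 both times. When the dependence was the same in both arms (true effect 0.30, r = 0.6), Δ was about 0 and both methods gave 0.302.

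**The case against.** The strongest defence is that randomisation makes the planned test valid and unbiased, and that in a repeated-measures ANOVA the baseline is already in the model as a time point, so its absence from a covariate list is natural. That stands as a defence of validity. It does not answer the loss of precision, which comes from using baseline in that role.

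The loss may also be small. At r = 0.8 the gap is about two percentage points, and if the plan silently assumed r = 0.75 it is about three (0.898 against 0.932). This is fair: the size depends on a correlation and a standardisation of d that the article does not give. The direction does not.

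The quoted method does not cover everything, since measures on a 3-point scale go to ordinal regression. That limits the ANOVA point to the remaining measures, but the covariate list makes no such distinction and omits baseline throughout.

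Three stronger readings are tempting, and the documents do not support them.

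- A reader might infer that the chosen ANOVA causes the loss of a fifth of the pupils. The sample size section introduces this loss with "As participant drop-out rates of 20% are common in randomised controlled trials" and already allows for it: 293 - 234 = 59. Complete-case ANCOVA would lose the same pupils, and the article states no rule for missing scores, which an analysis plan may well cover.
- A reader might infer that a mixed model with a common baseline mean would recover those pupils. Those without a post score have only a baseline, which adds nothing to the treatment contrast in such a model. In a simulated set of 293 with about 20% lacking a post score, its estimate and completer-only ANCOVA were identical (0.26957314).
- A reader might infer that any drop-out related to baseline biases the change score. Step 5 shows that the dependence must differ by arm.

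**Conclusion.** The point holds as one of efficiency. As written, the randomised comparison of every outcome analysed by repeated-measures ANOVA is a change-score test. Its variance exceeds that of baseline-adjusted ANCOVA at every r below 1; ANCOVA's is 35% lower at r = 0.3, 25% lower at 0.5, 15% lower at 0.7 and 10% lower at 0.8. With d in raw-score SD units, the power forgone runs from about 18 percentage points at r = 0.3 to about 2 at r = 0.8. These figures rest on equal SDs at the two time points, two-sided testing, 117 analysed per arm and an assumed r.

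A secondary benefit is conditional: if drop-out depends on baseline differently by arm, adjustment removes a bias of size (1-r)Δ that the change score carries. The planned analysis is not invalid. The change should be made because it improves precision at almost no cost.

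**What to change.** In Statistical methods, define the primary analysis of each primary outcome as the between-arm difference at 1 week post-intervention, by allocated arm, from a linear model adjusted for that outcome's baseline score and the five covariates already listed. Where ordinal regression is used for 3-point measures, include the baseline score there too. Keep repeated-measures ANOVA as a sensitivity analysis at most.

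The cost is a change of wording. The baseline scores are already collected before randomisation, the models run in the named software, and no further pupils or assessments are needed. If the plan relied on a particular baseline-to-post correlation, stating it would let readers see the size of the gain.
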